#### Cost-effectiveness and budget impact analysis

We will measure costs from a societal perspective, including health care costs and patient costs within and outside the hospital (see Additional file 2 for detailed information). Productivity costs will be ignored as the average age of patients participating will exceed the age of pensioning in the Netherlands. The patient questionnaire as well as follow-up data from hospital and GP medical records will be used for the calculation of total and per-patient costs. The EQ5D-5L scores retrieved from the questionnaire will be used to calculate quality-adjusted life-years (QALYs). Our patient outcome analysis will generate QALYs for different health states that will be used in health economic modelling, such as a complicated sepsis case (including ICU admission), hospital admittance for a suspicion of sepsis, and an infectious disease episode without hospital admission. Different scenarios with different levels of implementation of POCT for sepsis in general practice will be analysed and compared to standard of care: 100% use of the best performing testing strategy, 70%, 30%, and 0% use of POCT for suspicion of sepsis (the latter representing usual care). The budget impact will be assessed using the health economic model that will be built for the economic evaluation, and results will be analysed in a probabilistic way.

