### Candidate predictors

We selected nine clinical features and three blood tests as candidate predictors for the development of the clinical prediction model (Table 1). Parameters of widely used scoring systems such as the SIRS, qSOFA, and National Early Warning Score (NEWS) [18] were considered, as well as clinical features used in guidelines such as the Netherlands Triage Standard (NTS) and NICE Sepsis guideline [17]. Candidate predictors were selected if there was evidence to suggest that they might usefully contribute to the diagnosis of sepsis and if they can be easily and objectively measured by GPs.

**Table 1 Tab1:** Candidate predictors eligible for the selection in the prediction model

Type of predictor	Candidate predictor	Measurement method	Measurement unit	Used in
Clinical feature	Age	Inclusion date minus date of birth	Years	NICE guideline [17]
	Body temperature	Tympanic measurement	°C	SIRS [10], NEWS [18], NICE guideline
	Heart rate	IntelliVue MP2/X2	Beats/min	SIRS, NEWS, NICE guideline
	Respiratory rate	IntelliVue MP2/X2 or GP assessment	Breaths/min	SIRS, qSOFA, NICE guideline, NEWS
	Systolic blood pressure	IntelliVue MP2/X2	mmHg	qSOFA, NEWS, NICE guideline
	Peripheral oxygen saturation	IntelliVue MP2/X2	%	NEWS, NICE guideline
	Mental status	GP assessment	Normal/altered	qSOFA, NEWS, NICE guideline
	Rapid progression of illness in last 24 h	GP assessment	Yes/no	NICE guideline
	(History of) rigors in last 24 h	GP assessment	Yes/no	NTS [16]
Blood test	C-reactive protein (CRP)	Siemens, ADVIA Chemistry XPT	mg/l	
	Lactate	StatStrip Xpress	mmol/l	
	Procalcitonin (PCT)	Siemens, ADVIA Centaur XPT	ng/ml	

Candidate blood tests had to be currently used in the hospital setting for the diagnosis and/or prognosis of sepsis, and, preferably, to be available as a point-of-care (POC) test for reasons of implementation. CRP and lactate measurement are part of the standard care in patients with suspected sepsis during assessment in the Emergency Department (ED) in the Netherlands. Procalcitonin (PCT) is not routinely measured in most hospitals, but we decided to include PCT as a candidate predictor as PCT might be superior to CRP [19], and the NICE sepsis guideline recommends research to further evaluate the use of PCT POCT for diagnosing serious bacterial infection and initiating antibiotic therapy. CRP, lactate, and PCT are currently available as POC tests.

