#### Development of the prediction model

A multivariable penalized logistic regression model will be developed, based on the variables listed in Table 1, for predicting the primary outcome (sepsis within 72 h after inclusion). We will use a two-stepped approach entering and selecting clinical features first, and blood tests second. In both steps the selection of predictors will be based on a stepwise backward selection, using change in Akaike information criterion (AIC) for selecting the preferred model [24]. The goal is to generate an efficient model by eliminating variables that contribute little to the model’s performance, requiring only measurement of the most important variables in clinical practice.

Continuous predictors in the model will be assessed for linear relationship with the logit of the primary outcome. Transformation of the data and splines will be used if deemed appropriate based on distribution of the data.

The resulting prediction model will be the most accurate prediction model, by making use of continuous measurements of predictors and reflecting non-linear relationships by transformations or splines (optimal model). To make this model workable in daily clinical practice without electronic aids, a second model will be derived (clinical practice model) by categorising or stratifying predictors. Cutoffs for categorisation will be based on a combination of known and commonly used thresholds in clinical practice and optimal thresholds based on the data. This model simplification is likely to induce a performance drop with regard to the full model, which will be assessed during the analysis.

The above procedures will result in the following three models: (1) optimal model with clinical features only, (2) optimal model with clinical features and blood tests, (3) simplified model (with clinical features and blood tests).

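### The listed economic scenarios vary only the uptake of one testing strategy, so they inform budget impact but do not show whether adding blood tests to the clinical rule is worth the cost

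*Protocol article*

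**What the plan says.** The section *Cost-effectiveness and budget impact analysis* (Protocol article) plans costs from a societal perspective and QALYs from the EQ5D-5L by health state. It then fixes what is compared: "Different scenarios with different levels of implementation of POCT for sepsis in general practice will be analysed and compared to standard of care". The levels are "100% use of the best performing testing strategy, 70%, 30%, and 0% use of POCT for suspicion of sepsis", and the zero level is said to represent usual care. One model serves both purposes: "The budget impact will be assessed using the health economic model that will be built for the economic evaluation". Questionnaire and record data "will be used for the calculation of total and per-patient costs", with a pointer at the sentence on costs ("see Additional file 2 for detailed information").

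Two other sections matter. *Candidate predictors* states that "CRP, lactate, and PCT are currently available as POC tests", so the choice among three tests is a practical one. *Development of the prediction model* lists its three products: "1) optimal model with clinical features only, (2) optimal model with clinical features and blood tests, (3) simplified model (with clinical features and blood tests". The study will therefore have a rule that needs no blood test at all.

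The article does not define which strategy counts as best performing. The nearest criteria it states are the change in AIC (*Development of the prediction model*) and AUROC, calibration and Brier score (*Performance of the prediction model*).

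**The concern.** A cost-effectiveness analysis should help decide which strategy to adopt, and a budget impact analysis shows what adoption costs at different rates of use. The listed scenarios suit the second question. For the first they contain one contrast, the chosen strategy against usual care, at three levels of uptake.

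Two things are at stake.

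- A ratio against usual care averages over everything in the strategy. A panel of tests can look acceptable although most of its benefit comes from one component.
- The zero scenario is usual care, not the clinical rule without blood tests. Whatever GPs gain from scoring vital signs and history would be counted as a gain from POCT. The study sets out to investigate the potential benefit of that testing, so this is the contrast a reader will look for.

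**Working it through.** **Inputs from the article.** Uptake u = 1, 0.7, 0.3 and 0; comparator usual care; three candidate blood tests; a clinical-only model and two models with blood tests. The article gives no cost, QALY or ratio, so there is no figure to reproduce. All euro and QALY values below are assumptions for illustration.

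**Step 1: effect of uptake on the ratio.** Let C0, E0 be mean cost and QALYs under usual care and C1, E1 those under the testing strategy. I read the 70% and 30% levels as partial use of that same strategy, with the same case mix in tested and untested patients. Then

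C(u) = u·C1 + (1−u)·C0 and E(u) = u·E1 + (1−u)·E0,

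ICER(u) = u(C1−C0) / [u(E1−E0)] = (C1−C0)/(E1−E0) for every u > 0.

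With an assumed 50 euro and 0.005 QALY per patient, the ratio is 10,000 at 100%, 70% and 30%, and undefined at 0%. Only the budget moves: 50,000, 35,000, 15,000 and 0 euro per 1,000 patients.

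A probabilistic analysis behaves the same way, because net benefit is u(λΔE − ΔC) and its sign does not depend on u. With ΔC normal (mean 100, SD 80), ΔE normal (mean 0.006, SD 0.004), independent, and λ = 20,000, the simulated probability of being cost-effective was 0.573 at all three levels.

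**Step 2: fixed set-up cost F per 1,000 patients.** ICER(u) = (1,000·u·50 + F)/(1,000·u·0.005):

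| F (euro) | 100% | 70% | 30% |
|---|---|---|---|
| 0 | 10,000 | 10,000 | 10,000 |
| 5,000 | 11,000 | 11,429 | 13,333 |
| 20,000 | 14,000 | 15,714 | 23,333 |
| 50,000 | 20,000 | 24,286 | 43,333 |

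The ratio now depends on uptake, but only because the set-up cost is spread over more or fewer patients. Nothing in the table distinguishes CRP from lactate or PCT.

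**Step 3: what a comparison between strategies would show.**

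| Strategy | Added cost | Added QALY | Against usual care | Against previous row |
|---|---|---|---|---|
| Clinical rule | 20 | 0.0040 | 5,000 | 5,000 |
| + CRP | 35 | 0.0050 | 7,000 | 15/0.0010 = 15,000 |
| + CRP + lactate | 50 | 0.0058 | 8,621 | 15/0.0008 = 18,750 |
| + all three | 90 | 0.0060 | 15,000 | 40/0.0002 = 200,000 |

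The listed scenarios would report 15,000 for the full panel. Here the clinical rule alone supplies 0.004 of the 0.006 QALY, two thirds of the gain. The blood tests as a package cost (90−20)/(0.006−0.004) = 35,000 on top of it.

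**Step 4: range.** Hold the full panel at 90 euro and 0.006 QALY and the clinical rule at 20 euro, and vary the clinical rule's own gain:

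- 0.002 QALY: 70/0.004 = 17,500 for the blood tests
- 0.004 QALY: 70/0.002 = 35,000
- 0.005 QALY: 70/0.001 = 70,000

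The ratio against usual care is 15,000 in every case, so it does not reveal which of these applies.

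**The case against.** The strongest reply is that this is one paragraph of a condensed article under a joint heading. Uptake levels belong in a budget impact analysis, the article does not say that these scenarios are the only comparisons, and a fuller economic plan may hold more. That stands against any claim that the study will never compare tests. It does not remove the point: the section states the scenarios as the comparison with standard of care, without confining them to budget impact, and that stated set contains no contrast between strategies. Additional file 2 is not at hand, but it is cited for costs, not comparators.

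Three stronger readings are tempting and are not supported.

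- A reader might infer that the ratio cannot change with uptake. Step 2 shows that it does once there are fixed device or training costs, and a different case mix among users would also break proportionality.
- A reader might infer that the strategy will be picked on accuracy with cost ignored. The criterion is undefined. The nearest stated criteria have no cost term, but a choice on cost-effectiveness is not ruled out, and it would imply the missing comparison.
- A reader might count seven possible test combinations (2³ − 1) as left out. That is an upper bound on candidates. Backward selection may retain one test or none, which also makes a nearly useless extra test less likely, though not impossible.

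**Conclusion.** The point holds in limited form. As listed, the scenarios vary only uptake of one strategy against usual care. Under proportional costs and effects, the three non-zero scenarios repeat a single cost-effectiveness comparison. With fixed costs they differ, but still say nothing about what a blood test adds. Any benefit of the clinical-only rule would be credited to POCT.

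The algebra needs only proportionality and equal case mix. The size is unknown: 15,000 against 35,000 or 200,000 euro per QALY shows what could be hidden, not what is expected. The sample size, primary outcome and model development are untouched. The economic conclusion about which test, if any, to adopt is what depends on this.

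**What to change.** - Keep the 100/70/30/0% levels for the budget impact analysis, and say so.
- For cost-effectiveness, compare mutually exclusive strategies at full use: usual care, the clinical-features-only rule (the first of the three planned models), and the rule with each blood test or combination that the data support.
- Take the accuracy of each rule from its optimism-corrected, bootstrap-validated performance.
- Order the strategies by cost, remove dominated ones, and report fully incremental ratios or net benefit from the probabilistic model already planned.
- Define best performing, and state whether cost enters that choice.

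The cost is some extra model runs, including fits for test combinations outside the three planned models. No new data are needed. The downside is wide uncertainty between strategies that differ little, which the report should show.

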## Discussion

The TeSD-IT study is a diagnostic and prognostic study, designed for the development of a clinical prediction rule for the early recognition of sepsis in primary care. A limited number of nine clinical parameters and three blood tests were selected. This will enable us to construct the model using multivariable logistic regression techniques with 120 events included in the dataset. We realise the validity of rule of thumb of 10 event per variable is debated [27]. However, using an alternative sample size calculation suggested by van Smeden [28] results in a similar identical sample size of about 350 patients in case of 12 variables, an outcome rate of 0.35, and rMPSE set at 0.09. We have chosen to recruit patients in the setting of out-of-hours home visits performed by a GP. In this setting, GPs frequently encounter seriously ill patients in whom they instantly have to decide whether or not to refer the patient (immediately) to the hospital. A methodological advantage is that the required sample size is substantially lower than in other primary care settings with a lower incidence of sepsis. However, external validation in other settings and populations will be needed before implementing the clinical prediction rule more broadly.

The diagnosis of sepsis is not straightforward. In 2016, new consensus definitions for sepsis were published, which we try to implement as well as possible. As both the presence of infection as well as organ failure can be equivocal, we will use expert panels to determine the final outcome. The outcome should be clinically relevant for the GP. The rationale of the timeframe of 72 h is that patients who are found septic within this period after GP assessment would likely benefit from immediate hospital referral. Not all patients with organ failure need hospital treatment to recover, and not all patients with severe infections that are treated with intravenous antibiotic therapy have signs of organ failure. However, we believe the diagnosis of sepsis based on the Sepsis-3 definitions is the most relevant endpoint for GPs to differentiate between patients who are likely to benefit from immediate hospital treatment and patients who might be treated at home successfully. The expert panel will also rate the need for hospital treatment for every patient, regardless of the diagnosis. This will enable us to evaluate the effect of the new clinical prediction rule on medically unnecessary referrals.

The expert panels will be instructed to use the SOFA score (increase, due to infection, of ≥ 2 points from baseline) to define the primary outcome “sepsis within 72 h after inclusion”. This is consistent with the Sepsis-3 consensus definition and leads to an objective and reproducible endpoint in the absence of a gold standard. However, this approach introduces the risk of incorporation bias. Parameters included in the SOFA score are more likely to be predictive of sepsis in our model. However, the blood tests (CRP, lactate, and procalcitonin) are not included in the SOFA score, which limits the risk of incorporation bias for these tests. Furthermore, vital signs measured in the first 72 h will be used to calculate the SOFA score and not only at the time of inclusion.

Patients will receive a questionnaire at day 30 measuring EQ5D-5L. The results may be biased due to selective response and poor recall due to sepsis- or age-related cognitive impairment. Imputation of the missing answers on the questionnaires will reduce this form of bias as much as possible. Furthermore, the development of the clinical prediction rule is not affected, as the patient questionnaires will only be used for the cost-effectiveness analyses

To compare the performance of the new clinical prediction rule with usual care, not only the decision to refer the patient to the ED, but also the assessment of the GP of the likelihood of sepsis on a scale from 0 to 10 and the presence of a “gut-feeling something is wrong” will be used. We will examine if the prediction rule will outperform those assessments of the GP in order to likely improve the usual care.

Only three candidate blood tests were selected for the development of the prediction rule. Various other biomarkers have promising diagnostic and/or prognostic properties in patients with suspected sepsis [29, 30]. At the start of this study, sufficient evidence of the additional diagnostic and/or prognostic value above lactate, CRP, and PCT was lacking. However, sufficient blood samples will be stored for retrospective testing of multiple additional biomarkers.

Although to our best knowledge no clinical prediction rules for sepsis in primary care were previously developed, several sepsis screening tools were published for the ambulance setting [31]. However, none of those have adequate inclusion criteria, data collection, and clinically relevant endpoints for use in the primary care setting.

## Data Availability

Data will be made available from the corresponding author upon reasonable request after completion of the study.

## Abbreviations

AIC: Akaike information criterion
CRP: C-reactive protein
ED: Emergency department
GP: General practitioner
ICU: Intensive care unit
NEWS: National Early Warning Score
NTS: Netherlands Triage Standard
PCT: Procalcitonin
POC(T): Point-of-care (testing)
AUROC: Area under the receiver-operator characteristic
SIRS: Systemic inflammatory response syndrome
(q)SOFA: (quick) Sequential organ failure assessment score
QALY: Quality-adjusted life year
